## **7.6.3 Laboratory procedures**

### **7.6.3.1 Sample Receipt**

The central laboratory will be responsible for performing sample, documentation and eligibility checks of all self-samples received at the laboratory in accordance to cervical screening programme guidelines and the YouScreen Laboratory Manual to determine whether a sample is valid or invalid for HPV testing.

The central laboratory will also be responsible for maintaining electronic records of whether participants have consented to residual samples storage.

### **7.6.3.2 HPV Testing and Result Reporting**

Valid samples will be tested for HPV using the Roche cobas® 4800 platform detailed further in Section Roche cobas 4800 System8.2. The cobas® 4800 Human Papillomavirus (HPV) Test is a qualitative in vitro test for the detection of Human Papillomavirus in patient specimens. The test utilises amplification of target DNA by the Polymerase Chain Reaction (PCR) and nucleic acid hybridisation for the detection of 14 high-risk (HR) HPV types in a single analysis. The test specifically identifies (types) HPV16 and HPV18 while concurrently detecting the rest of the high-risk types (31, 33, 35, 39, 45, 51, 52, 56, 58, 59, 66 and 68) at clinically relevant infection levels. The cobas® assay simultaneously tests for human beta-globin as an internal control of sufficient specimen cellularity. In addition, a positive and negative control specimen will be included in each run.

HPV testing will be performed with the liquid-based cytology (LBC) ThinPrep platform (PreservCyt) by the HSL laboratory. Samples will be prepared and processed following the Roche company guidelines.

The laboratory will record presence of human beta-globin, HPV result including HPV type (16/18 and other), although only HPV results without type will be reported to GPs and to women.

Results will be recorded in the usual NHS laboratory electronic LIMS database. Results will be reported from the laboratory to the GP practices using electronic links and automatically coded into EMIS Web if possible. Where electronic lab links are not available results will be sent via letter to the GP Laboratory Information System (LIMS).

The laboratory will stop analysing self-samples one month after the last kit has been sent out (including repeat kits for unavailable results). Women will be informed of this when they receive their kit.

## **7.7 Residual samples**

All women will be asked to opt in by completing an initials box on their lab request/consent form to allow their residual samples to be stored with their personal details removed for future ethically

approved research. Samples will be discarded by the central laboratory according to local procedures after HPV result reporting unless the initials box on the lab request/consent form is completed to indicate their consent.

Residual samples will comprise of human DNA in the leftover elute from HPV testing on self-samples. After HPV results have been reported, residual samples belonging to participants that have opted in for residual sample storage, will be de-personalised by the central laboratory (personal identifiers removed, leaving only barcode or unique kit ID) and stored refrigerated (2-8 °C) pending shipment to the Guy's and St Thomas' Research Biobank (HTA licence number 12121) for storage pending future ethically approved research. The de-personalised residual samples will be sent by the central laboratory under the conditions defined in the material transfer agreement to the biobank facility.

At the end of the trial, residual samples will remain in storage under the Guy's and St Thomas' institutional HTA license, pending use for possible future ethically approved research. Any future research on residual samples will be in research to inform management for cervical screening in the future and will be overseen by the YouScreen Chief Investigator. Results will not impact clinical management for women in the trial.

## **7.8 Follow up**

### **7.8.1 Women who return a self-sample**

#### *7.8.1.1 Clinical Follow up*

All women who return a self-sample will be passively followed up for the duration of the trial, to obtain data on subsequent cervical screening tests, referrals to colposcopy and/or diagnoses of CIN2+. At the end of recruitment, we have factored in 6 months follow up time to allow data collection for self-sample HPV positives. Individual participant clinical follow-up length for self-sample screen positives during the current protocol will depend on the point at which they are enrolled and will range from 6-18 months. This will be carried out using NHAIS and GP record data.

#### *7.8.1.2 Passive Long Term follow up*

After the trial has ended we will continue to passively observe those enrolled in the trial through their cancer screening, cancer registration and other health related records through central registries at NHS Digital and Public Health England. This will include depersonalised data recorded on participants' cervical cancer or CIN3 diagnoses, tumour and individual characteristics, their interactions with the NHS as part of their cancer pathway. Linkage between these datasets will be conducted using privacy conserving methods (OpenPseudonymiser) to minimise the transfer of personal confidential data. Where available, molecular data recorded by NCRAS will also be analysed to support analysis of the epigenetics of cervical cancer within the population.

This will enable us to carry out long term follow up analysis to assess "longterm" coverage at 13 months after the trial has ended and on CIN2+ and cervical cancer rates in women who return a self-sample at approximately 3 and 6 years after the trial has ended. As the YouScreen samples will be the only self-samples recorded in NHAIS over the trial period, it should be straightforward for NHS Digital to provide us with aggregate anonymous data on the numbers of relevant women screened in NHAIS. The precise mechanism for collecting longterm follow up data at 3 and 6 years is dependent on future funding and therefore will be decided at a later date. However, we will request permission from the participants to allow for passive long term follow up via the colposcopy hospital records (e.g. Cyres database) and if feasible and from the National Cancer Registration and Analysis Service (aggregate anonymous data).

### **7.8.2 All women offered a kit**

#### *7.8.2.1 Passive long term follow up*

After the current trial has ended we also plan to collect follow up data on all women offered a kit from NHAIS to examine the impact of self-sampling on long-term coverage at 13 months and at approximately 3 and 6 years after the trial end (as a minimum we will examine long-term coverage at 13 months after last woman was sent/given a kit (NHAIS data and GP medical record data). This will allow us to assess any "nudge" effect that the offer of self-sampling has on conventional

screening uptake, and whether or not the women who uptake self-sampling would have come for screening in any case.

### **7.8.3 All eligible women**

#### **7.8.3.1 Passive long term follow up**

We will also assess long-term coverage for all eligible women at 13 months and at approximately 3 and 6 years after the trial end (as a minimum we will examine long-term coverage at 13 months after last woman was sent/given a kit (NHAIS data and GP medical record data) . This will comprise aggregate anonymous data from NHAIS.

### **7.9 Withdrawal criteria**

Participants will be free to withdraw from the trial at any time without giving reasons and without prejudicing their further treatment and will be provided with a contact point where they may obtain further information about the trial and the withdrawal process. If participants choose to withdraw, the trial team would include them in the assessment of self-sampling and self-sampling HPV test result uptake data for reporting. Participants will be made aware (as detailed in the patient information booklet) that any samples that have been taken as part of the trial will continue to be analysed and data retained in the project however no new data will be collected (except anonymous aggregate data for which consent is not required). Residual samples can be requested to be destroyed.

Throughout the duration of the trial, participants will be able to visit the trial small c website for full information including accessing up-to-date contact details and the process for withdrawing their consent for the trial.

### **7.10 End of Trial**

The end of the active recruitment of the trial will be defined as either when a minimum of 10,000 kits have been returned or at 12 months after study start, whichever is earliest.

The trial will end once a minimum of 6 months of follow-up data (6 months from the last participant recruited) for women testing HPV positive on a self-sample have been received.

The Chief Investigator will inform the REC of the end of the trial within 90 days of its completion. A summary of the final research report will be sent to the REC within 12 months of the end of the trial

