| Inclusion Criteria  | 
 
• Women <math>\geq 25</math> and <math>\leq 64^*</math> years old, and
 
• Eligible for cervical screening under the NHS CSP in England, and
 
• At least 6 months overdue cervical screening; and
 
• Registered at a participating GP practice
 
                                                                                                                                                                                                                                                                                                                                                                                                                                                                                         |                 |
| Exclusion Criteria  | 
 
• Women unable or unwilling to provide informed consent
 
• Women under the care of colposcopy within the last 36 months and/or due for a test of cure (HPV test to confirm if a woman has been successfully treated after treatment for cervical abnormalities)
 
                                                                                                                                                                                                                                                                                                                                                                                                                                                                                       |                 |
| Planned sample size | 
We expect up to ~10,000 women will return a self-sample
 
Assumptions:
 
 
• ~50% (106/212) of eligible GP practices recruited
 
• 9 months average recruitment period at GP practices
 
• An estimated 31,000 participants will receive self-sampling kits: 
 
○ 19,000 via direct mail out
 
○ 12,000 kits accepted opportunistically in GP primary care
 
 
 
• Estimated uptake: 15% for direct mail-out and 50% of those offered opportunistically
 
                                                                                                                                                                                                                       |                 |

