#### CE Marking and intended use:

The cobas 4800 HPV Test is CE marked as an in vitro diagnostic medical device (according to the In-Vitro Diagnostic Medical Devices Directive 98/79/EC).

Indications for use of the cobas® 4800 HPV Test are:

- (a) *The cobas® 4800 HPV Test is indicated for use in screening patients with ASC-US (atypical squamous cells of undetermined significance) cervical cytology results to determine the need for referral to colposcopy.*
- (b) *The cobas® 4800 HPV Test is indicated for use in screening patients with ASC-US cervical cytology results to assess the presence or absence of high-risk HPV genotypes 16 and 18.*
- (c) *The cobas® 4800 HPV Test is indicated for use adjunctively with cervical cytology to assess the presence or absence of high-risk HPV types.*
- (d) *The cobas® 4800 HPV Test is indicated for use adjunctively with cervical cytology to assess the presence or absence of HPV genotypes 16 and 18.*
- (e) *The cobas® 4800 HPV Test is indicated for use as a first-line primary screening test to identify women at increased risk for the development of cervical cancer or presence of high-grade disease.*
- (f) *The cobas® 4800 HPV Test is indicated for use as a first-line primary screening test to assess the presence or absence of HPV genotypes 16 and 18.*

As such the cobas 4800 HPV test will be used **outside** of its licenced indication for the trial and will be considered to be exempt from the directive under the 'in-house exemption' to the Medical Devices Regulations 2002. Full details can be found in section

**Supply:** Health Service Laboratory will procure the cobas 4800 HPV test and associated reagents from Roche for analysis of 10,000 (+/- 10%) samples.

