## 9 STATISTICAL CONSIDERATIONS

### 9.1 Sample size considerations

This is a feasibility trial of the implementation of a new self-sampling pathway that is not designed to detect a difference between two arms. Rather, to estimate the increase in coverage associated with offering self-sampling to nonattenders, therefore, formal power calculations are not appropriate. In

addition, the trial aims to recruit as many women as possible that the budget will allow. Our budget allows for a return of approximately 10,000 samples and issuing of circa 31,000 kits.

According to the NHAIS 2017/18 data available online from the National General Practice Profiles (<https://fingertips.phe.org.uk/profile/general-practice>), across the five CCGs included in our trial there are 212 GP practices and 190,579 women who are  $\geq 6$  months overdue for cervical screening. Assuming 50% (106/212) of GP practices agree to take part, there would be approximately 95,000 ( $0.50 \times 190,579$ ) eligible women (i.e. women aged 25-64 eligible for cervical screening who are overdue by at least 6 months).

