### 9.1.1 Direct Mail-out

Assuming 106 GP practices recruit women for an average of 9 months (GP practices will recruit for a minimum of 6 months and a maximum of 12 months given that study set-up at each practice will be staggered over a 6 month period) and 20 women reach the 15 month anniversary at each practice each month, approximately 19,000 women will be sent kits during the trial. Table 2 below provides the expected 95% confidence intervals for various uptake levels over an average of 9 months recruitment period. We have estimated that 15% of women who receive a kit via direct mail-out will return a self-sample (i.e. ~2,800 women will return a self-sample over an average of 9m).

**Table 2 Expected 95% confidence intervals for different proportions of women who return a self-sample based on 106 GP practices over a 9-month average recruitment period**

| Uptake among those offered kits | 95%CI     |
|---------------------------------|-----------|
| 10%                             | 9.6-10.4  |
| 15%                             | 14.5-15.5 |
| 20%                             | 19.4-20.6 |
| 30%                             | 29.3-30.7 |

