### 9.1.2 Opportunistic offering of self-sampling

With an estimated 106 GP practices participating, there would be some 95,000 ( $190,579 \times (106/212)$ ) women eligible for opportunistic offering of kits. Based on our previous studies(16, 37)) we estimate that ~60% (57,000) will consult their GP practice over 9-12 months, some 17,100 (30%) will be offered a self-sampling kit and of those offered, ~12,000 (70%) will accept. We estimate that a total of ~8,500 would return a self-sample for HPV testing (50% of those offered i.e.  $17,000 \times 0.5$ ). Therefore, the proportion of women  $\geq 6m$  overdue cervical screening who will return a sample when opportunistically offered a kit (i.e.  $\approx 8,500/17,000$ ) could be estimated with a 95% confidence interval of width  $\pm 1.0\%$ .

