### 9.1.3 Questionnaire-based sub-study

As the trial is designed to be descriptive, a formal power calculation is not possible. A previous study in Westminster, London(18) had a survey response rate of 97% among the 6% of women who completed a self-sample kit, and just under 1% for those who did not send back a kit. We therefore expect a very low response rate in women who do not return the kit, making statistical comparisons between completers and non-completers inappropriate. However, we plan to explore demographic patterns of PAPM stage, previous barriers and confidence in completing the kit (e.g. by ethnicity and level of deprivation) within the completer and (to a lesser extent) the non-completer groups, and to do this, we anticipate needing a relatively large sample.

We have allowed for a high response rate (90% for kit completers; 10% for non-completers) to avoid under-funding. This would yield a sample of ~5,500 kit completers and ~2,500 non-completers but we anticipate the actual sample size is likely to be somewhat lower.

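### Planned numbers of returned self-samples do not agree: about 10,000 in the summary, 11,300 from the pathway projections, and 6,200 implied by Table 3

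*Protocol*

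**What the plan says.** **Headline total.** The trial summary states: "We expect up to ~10,000 women will return a self-sample". Beneath it are listed 106 practices, a 9-month average run, 19,000 mailed kits, 12,000 kits accepted in practices, and uptake of 15% (mail-out) and 50% (of those offered opportunistically). Section 9.1 gives the same total as a budget figure: "Our budget allows for a return of approximately 10,000 samples and issuing of circa 31,000 kits".

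**Pathway projections.** For the mail-out, section 9.1.1 projects about "2,800 women will return a self-sample over an average of 9m". For the opportunistic route, section 9.1.2 says: "We estimate that a total of ~8,500 would return a self-sample for HPV testing".

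**Sub-study.** Section 9.1.3 assumes that 90% of kit completers and 10% of non-completers answer the questionnaire, and concludes: "This would yield a sample of ~5,500 kit completers and ~2,500 non-completers". Table 3 gives 5,580 and 2,480, total 8,060, from 31,000 sent.

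**Recruitment end.** Section 7.10 ends active recruitment "when a minimum of 10,000 kits have been returned or at 12 months after study start, whichever is earliest". Section 9.1.1 says "GP practices will recruit for a minimum of 6 months and a maximum of 12 months", and the summary's duration entry gives the same range with a 9-month average.

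**Laboratory supply.** Section 8.2.1 plans reagents "for analysis of 10,000 (+/- 10%) samples"; section 8.2 gives the same quantity for consumables.

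**The concern.** One quantity, the number of samples returned, drives the recruitment stop, the laboratory supply and the sub-study size, yet it takes different values in different places. Only 10,000 is printed as a total. The figure of 11,300 is the sum of two printed components, and 6,200 is what Table 3's percentages require. The status of 10,000 is also unclear: an upper expectation in the summary, a budget in section 9.1, and a minimum that triggers the end of recruitment in section 7.10.

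At stake are the stated sample sizes and the sub-study funding. Section 9.1.3 says its response rates were set high so as not to under-fund the questionnaire work, but the number of completers to which they are applied is too low for the rest of the protocol.

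**Working it through.** **1. Reproduce the components (sections 9.1, 9.1.1, 9.1.2).**
- Mail-out kits: 106 × 20 per month × 9 months = 19,080 (stated about 19,000).
- Mail-out returns: 19,080 × 0.15 = 2,862 (stated about 2,800).
- Opportunistic offers: 190,579 × 0.5 × 0.6 × 0.3 = 17,152 (stated 17,100).
- Accepted: 17,152 × 0.7 = 12,006 (stated about 12,000).
- Opportunistic returns: 17,152 × 0.5 = 8,576 (stated about 8,500).

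Each component reproduces.

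**2. Sum them.** 2,800 + 8,500 = 11,300; unrounded, 2,862 + 8,576 = 11,438. That is 13% to 14% above 10,000. Applying the 50% to accepted instead of offered kits gives 19,000 × 0.15 + 12,000 × 0.5 = 8,850, which is not 10,000 either.

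**3. Remove double counting (assumption: the pathways are independent).** Mail-out women are a sub-group of the eligible women (section 6.1), and the laboratory rejects a second self-sample in the same round (section 7.2.2). Women counted twice: 2,850 × 0.6 × 0.3 × 0.5 ≈ 257. The total becomes about 11,040 to 11,180.

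**4. Back-calculate Table 3.**
- Completers: 5,580 / 0.90 = 6,200.
- Non-completers: 2,480 / 0.10 = 24,800.
- Sum: 31,000 exactly, so the base is 6,200 / 31,000 = 20% completion.

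This is 38% below 10,000, 45% below 11,300, and below the 8,500 opportunistic returns alone. With 2,800 mail-out returns, only 3,400 would be left for the opportunistic route: 3,400 / 17,000 = 20% of those offered, against the stated 50%.

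**5. Recompute Table 3 at its own rates, 31,000 kits held fixed.**

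| Returns | Completers (90%) | Non-completers (10%) | Total |
|---|---|---|---|
| 6,200 (as printed) | 5,580 | 2,480 | 8,060 |
| 10,000 | 9,000 | 2,100 | 11,100 |
| 11,300 | 10,170 | 1,970 | 12,140 |

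**6. Time basis.** Section 9.1.2 lets the 60% consult over 9 to 12 months, while section 9.1.1 uses 9. Assuming linear accrual and a 9-month average run:
- 9-month basis: 8,576 + 2,862 = 11,438.
- 10.5-month basis: 8,576 × 9/10.5 + 2,862 = 7,351 + 2,862 = 10,213.
- 12-month basis: 8,576 × 9/12 + 2,862 = 6,432 + 2,862 = 9,294.

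**7. Stop rule, conditional.** Assume the 9-month rate, starts spread evenly over 6 months, and no delay between kit and return.
- Average run when 10,000 is reached: 9 × 10,000/11,300 = 7.96 months (7.87 with 11,438).
- Calendar time: 3 + 7.96 = 10.96 months (10.87).
- Last-starting practice: 10.96 − 6 = 4.96 months (4.87).
- Mailings by then: about 16,700 to 16,900; all kits: about 27,100 to 27,400.

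A mean return delay of 1 month moves the stop to 11.87 to 11.96 months, and 1.5 months takes it past 12. On the 12-month basis in step 6, or on Table 3's 6,200 (10,000 reached only at an average run of 9 × 10,000/6,200 = 14.5 months), the 12-month limit applies.

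**8. Precision.** At 15% uptake the 95% half-width is 0.51 points with 19,080 kits and 0.54 with 16,885. For the opportunistic route it is 0.75 points with 17,000 offers and 0.80 with 15,044.

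**The case against.** The best defence is that 10,000 is a budget cap, not a forecast. The summary words it as an upper figure, section 9.1 ties it to money, and the same section says that a power calculation does not apply to this trial. Further, the 9-to-12-month window in section 9.1.2 yields about 9,300 to 11,400 returns, which brackets 10,000. These arguments soften the gap between 10,000 and 11,300 but do not close it: the summary sets 10,000 above the same assumptions from which section 9 prints 2,800 and 8,500, and no time basis is given that would make the figures agree. They do nothing for Table 3, since none of these readings gives 6,200. The remark in section 9.1.3 that the real sample may be smaller does not explain the low number of completers. It is fair to add that Table 3 is a funding allowance for a descriptive sub-study.

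A reader might infer more: that the 10,000-return stop will end recruitment in month 11, deny the last practices their 6 months, and still exhaust the laboratory supply. The documents do not support that as a firm conclusion. It needs the fastest accrual in the stated window and no return delay, although uptake is measured at 30 and 90 days. Section 4.1 expects the opportunistic offer, which supplies most returns, to start later than the mail-out. Section 4.2 allows recruitment at a practice to run longer or shorter according to uptake. The excess over the supply ceiling of 11,000 is 300 to 438 samples before overlap is removed and about 40 to 180 after, and it vanishes on the slower time bases.

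**Conclusion.** The planned return numbers are inconsistent as written. The pathway projections exceed the headline by 13% to 14% on the printed figures, or 10% to 12% after removing double-counted women under independence. Table 3 rests on 6,200 completers, 38% to 45% below the main-trial figures, and understates its own questionnaire total by 3,040 to 4,080. The Table 3 result needs no timing assumption.

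The conflict between the section 7.10 stop and the 6-month minimum and 9-month average is conditional. It arises at the 9-month rate with even starts and no return delay, and disappears with slower accrual or a delay of about a month. The passages should still be reconciled, because the protocol's own figures allow the conflict. The effect on the precision of uptake is negligible either way, so this is a matter of correct planning figures and does not threaten the primary estimate.

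**What to change.** - State one expected total of returned samples in the summary and section 9.1, with its time basis (9 months, or 9 to 12 for the opportunistic route) and with women counted once.
- Say whether 10,000 is a forecast or a budget cap, and use the same description in the summary, section 7.10 and section 9.1.
- Recompute Table 3 and the text of section 9.1.3 from that total: about 9,000 + 2,100 = 11,100 questionnaires for 10,000 returns, or 10,170 + 1,970 = 12,140 for 11,300.
- Match the laboratory quantity in sections 8.2 and 8.2.1 to the same total.
- Reconcile section 7.10 with the 6-month minimum and 9-month average, stating which gives way if the count is reached first.
- In the summary, call the 31,000 kits, not participants. Section 7.2.2 lets a woman receive both kinds; on the plan's rates, assuming independence, about 19,000 × 0.6 × 0.3 × 0.7 ≈ 2,400 would.

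The cost is editing of the protocol. No extra women are needed. The questionnaire budget may have to rise, and some stated figures will look less favourable.
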